#### Harms monitoring and safety procedures

##### Real-time monitoring during exercise

The supervising physiotherapist has authority to terminate the exercise session immediately if any safety concern arises. Medical support is available immediately if needed, with emergency equipment accessible per hospital protocol. Participants have the explicit right to request session termination at any time for any reason, without penalty or compromise to clinical care.

##### Post-session assessment

Vital signs (BP, HR, RR, SpO₂) will be assessed at 1-min post-exercise and monitored continuously until participant hemodynamic stability is confirmed (typically 5 min). Participants will be instructed to report any delayed adverse symptoms (occurring > 1 h after exercise completion) within 24 h via telephone contact with research team. Contact information will be provided to all participants before exercise begins.

##### Serious adverse event reporting

Any serious adverse event (as defined in Reporting Approach section) occurring during or within 24 h post-exercise will be reported to the principal investigator immediately (within 2 h of identification). Serious adverse events will be reported to the Research Ethics Committee of UNIFESP within 48 h. All events will be assessed for temporal and causal relationship to study procedures using standardized relatedness categories (definite, probable, possible, unrelated). If a pattern of concerning adverse events emerges (≥ 2 serious events potentially related to study procedures), the principal investigator will assess whether Data Safety Monitoring Board review or study pause is warranted.

#### Data analysis approach for harms

Adverse event rates (number of events, number of participants experiencing events) will be compared between the immersive VR intervention group and the standard exercise control group using chi-square tests for between-group differences in event incidence. Between-group differences in adverse event rates will be examined, with particular attention to VR-specific harms (cybersickness symptoms). Within-group adverse event trends will be monitored during recruitment, with events documented by participant sequence and group assignment to identify any temporal patterns suggesting emerging safety signals. Any suspected safety signals (unexpected increase in serious adverse events, or higher-than-anticipated adverse event rate in one group) will be reviewed by the research team and discussed with the Ethics Committee for determination of appropriate action (e.g. protocol modification, participant notification, study pause or continuation with enhanced monitoring).

### Participant timeline {18}

**Table Tabb:** 

	**TRIAL PERIOD (b)**			
	**Enrolment**		***Intervention***	***Post-Exercise/Close-out***
**TIMEPOINT**	***-t***_***i***_** to 0**	**0**	***t***_***1***_	***t***_***2***_
***ENROLLMENT***				
Eligibility screening	X			
Informed consent	X			
Randomization		X		
**INTERVENTION/COMPARATOR (a,c)**				
Cycle-ergometer + VR (intervention)			X	
Standard cycle-ergometer exercise (Comparator)			X	
**BASELINE ASSESSMENTS (e)**				
Demographics and clinical history		X		
HADS (d)		X		
Baseline vital signs (BP, HR, SpO₂, RR)		X		
Modified Borg Scale (RPE)				
Baseline 12-lead ECG		X		
**DURING EXERCISE ASSESSMENTS (f)**				
BP			X	
HR			X	
SpO₂ %			X	
Modified Borg Scale (RPE)			X	
Continuous 12-lead ECG monitoring			X	
**POST-EXERCISE ASSESSMENTS**				
Total exercise time (minutes) (g)				X
Recovery vital signs				X
SUS—VR group only (i)				X
PACES (h)				X
Adverse events assessment (j,k)				X

a) Single-session design: Only ONE exercise session per participant during hospitalization.

b) Timepoints: Enrollment → Randomization → Intervention → Post-Exercise/Close-Out. No follow-up.

c) Both groups identical protocol except: VR group receives immersive VR headset; control group receives standard cycle ergometer.

d) Hospital Anxiety and Depression Scale (HADS): 14-item self-report questionnaire assessing anxiety (7 items, score 0–21) and depression (7 items, score 0–21) during acute hospitalization [24, 25]

e) Continuous vital signs monitoring: Blood pressure (BP, mmHg, systolic/diastolic), heart rate (HR, bpm), peripheral oxygen saturation (SpO₂, %) and respiratory rate (RR, breaths/min) recorded every minute throughout exercise and recovery period via automated monitors and continuous 12-lead ECG.

f) Session termination criteria: Immediate termination triggered if Rating of Perceived Exertion (RPE) ≥ 5 (‘hard’ intensity) OR if any safety threshold exceeded: BP > 200 mmHg or < 80 mmHg (systolic), HR > 130 or < 40 bpm,SpO₂ < 85% or ST-segment changes on ECG.

g) Total exercise time: Cumulative pedaling time (minutes) from initiation to termination.

h) Physical Activity Enjoyment Scale (PACES): 18-item questionnaire (score 18–80); higher = greater enjoyment [18, 19]

i) System Usability Scale (SUS10-item questionnaire (score 0–100); ≥ 68 indicates above-average usability; ≥ 70 considered acceptable for clinical implementation [20, 21]

j) Adverse events: Serious (requiring intervention) vs. non-serious. Documented immediately post-exercise.

k) Real-time data collection: All vital signs, RPE, observations recorded by physiotherapist on paper CRF during exercise; transferred to REDCap same day.

### Sample size {19}

The sample size was estimated for adult inpatients with clinical HF decompensation who are hemodynamically stable and meet the study’s eligibility criteria. This is a prospective, randomized trial with a total sample of 60 participants (30 per group, control and intervention), defined by computer-generated 1:1 with no stratified.

Calculations were performed in G*Power (v3.1.9.2) assuming a superiority design with an independent-samples *t* test as the primary analysis. Based on prior VR exercise studies [11, 17, 26], we assumed a moderate effect size (Cohen’s *d* = 0.65) for the primary outcome (total exercise duration completed). With alpha set at 0.05 (two-tailed), beta at 0.20 (80% power) and assuming 10% dropout, the required sample size was determined to be 30 participants per group (*n* = 60 total). Secondary per-protocol analysis will include participants who completed the entire exercise session without unplanned termination.

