### Statistical methods

#### Statistical methods for primary and secondary outcomes {27a}

Analyses will be performed using SPSS Statistics v25.0 with significance level α = 0.05 (two-tailed). Primary outcome (total exercise duration) will be compared between groups using independent-samples *t* test, or Mann–Whitney *U* test if normality is violated (Shapiro–Wilk *p* < 0.05). Secondary outcomes will be compared using appropriate parametric or non-parametric tests. Likert-scale items will be analyzed using Mann–Whitney *U* tests. Descriptive statistics (means ± SD, medians [IQR]) will characterize all outcomes.

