## Future directions and expected outcomes

Our pilot study [17] demonstrated feasibility of immersive VR exercise in hospitalized HF patients. This REVIVE-HF trial represents a rigorous advancement with adequate sample size, randomized design and predefined outcomes. We expect the VR group to achieve longer exercise duration and higher enjoyment (PACES) and usability (SUS) scores compared to controls. If confirmed, this protocol could be adapted to other hospital contexts and incorporated as a complementary resource in cardiac rehabilitation programs, contributing to innovation in acute care.

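### The stated inputs require 39 evaluable (44 randomised) per group, not 30; at d = 0.65, 30 per group gives about 70% two-tailed power, or 65% after the plan's own dropout

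*Protocol article*

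**What the plan says.** Sample size {19} gives every input to the calculation. It names G*Power, a superiority design and an independent-samples t test. For the effect it says: "we assumed a moderate effect size (Cohen’s *d* = 0.65) for the primary outcome (total exercise duration completed"). The error rates and the result follow in one sentence: "With alpha set at 0.05 (two-tailed), beta at 0.20 (80% power) and assuming 10% dropout, the required sample size was determined to be 30" per group, 60 in total. Allocation is 1:1.

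The analysis section, Statistical methods for primary and secondary outcomes {27a}, repeats the sidedness: "Analyses will be performed using SPSS Statistics v25.0 with significance level α = 0.05 (two-tailed"). It keeps the t test as the first choice for the primary outcome, with a Mann–Whitney test if normality is rejected. The missing-data section {27c} specifies a complete-case analysis when the primary outcome is missing, so each loss reduces the number analysed.

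Future directions and expected outcomes then relies on the result: "This REVIVE-HF trial represents a rigorous advancement with adequate sample size".

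**The concern.** The effect size is standardised, so test, d, alpha, sidedness, power and dropout together fix the answer. No standard deviation or outside source is needed, and no separate analysis plan could change what these inputs yield. For two arms, 30 per group is visibly too few for a two-tailed test at d = 0.65 with 80% power, before any allowance for dropout.

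At stake is how the result will be read. A reader who trusts the 80% will take a non-significant result as fairly strong evidence against an effect of d = 0.65. If power is 65% to 70%, the trial would miss such an effect about one time in three, not one in five. The error also runs in the direction that favours the design, and the description of the sample as adequate rests on it. It does not affect the type I error or the validity of the planned test.

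**Working it through.** **Inputs** (all from Sample size {19}; sidedness confirmed in {27a}): independent-samples t test, 1:1, d = 0.65, alpha = 0.05 two-tailed, power 0.80, dropout 10%, stated result 30 per group.

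**Step 1. Try to reproduce 30, normal approximation.**
n per group = 2 (z_alpha + z_beta)² / d²
- Two-tailed: 2 × (1.960 + 0.842)² / 0.65² = 2 × 7.85 / 0.4225 = 37.2, so 38.
- One-tailed: 2 × (1.645 + 0.842)² / 0.4225 = 2 × 6.18 / 0.4225 = 29.3, so 30.

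**Step 2. Exact noncentral t, the calculation that G*Power makes for this test.** Power is the probability that a t variable with 2n − 2 degrees of freedom and noncentrality d√(n/2) exceeds the critical value.

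| Variant at d = 0.65, 80% power | n before dropout | n / 0.9 | n × 1.1 |
|---|---|---|---|
| Two-tailed (as stated) | 38.14, so 39 | 43.3, so 44 | 42.9, so 43 |
| One-tailed | 29.97, so 30 | 33.3, so 34 | 33 |

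No two-tailed variant gives 30, with or without dropout. Of the variants tried at d = 0.65 and 80% power, only the one-tailed calculation with no dropout allowance matches.

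The shortfall against the stated claim is 44 − 30 = 14 per group (28 in total), or 39 − 30 = 9 per group (18 in total) if dropout is ignored.

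**Step 3. Two-tailed power that the planned numbers provide at d = 0.65.**
- 30 analysed per group: noncentrality 0.65 × √15 = 2.52; exact power 69.7% (normal approximation 71.1%).
- 27 analysed per group (30 less 10%): noncentrality 0.65 × √13.5 = 2.39; exact power 65.0% (normal approximation 66.6%).
- Type II error: 100 − 69.7 = 30.3% and 100 − 65.0 = 35.0%, against the stated 20%.

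For comparison, one-tailed power with 30 per group is 80.0%.

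**Step 4. Effect detectable with 80% two-tailed power.**
- 30 per group: d = 0.736, about 0.74.
- 27 per group: d = 0.777, about 0.78.

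**Step 5. Does the fallback test rescue the figure?** If the Mann–Whitney test is used and its relative efficiency is taken as 3/π (an assumption, its value under normality), power is about 68% with 30 per group and 63% with 27. It does not.

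**The case against.** The best defence is that loss will be small. There is one session and no follow-up, and a participant who stops early still contributes an exercise time, so early termination is not dropout. That stands: 65.0% is a planning case at the protocol's own 10%, and 69.7% is the no-loss case. Some loss is possible, since participants with significant discomfort during VR familiarisation do not go on to exercise. Even with none, power is about 10 points below the claim.

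A second defence is that a superiority question may be tested one-sided. Both the sample-size section and the analysis section say two-tailed, so this does not help. Nor does the sample-size section present 30 as a feasibility limit; it presents it as the number required.

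It can also be said that the article calls its evidence preliminary in the abstract and foundational under Trial design, so it does not rest everything on this number. That is fair, and no claim to definitive efficacy is needed here. A misstated power is enough.

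Three stronger readings are tempting but not supported:
- A reader might infer that a one-tailed option was selected by mistake. The numerical match is exact, but nothing in the article mentions a one-tailed calculation, so the cause remains an inference.
- A reader might infer that power is lower still because five 3-minute blocks cap pedalling at 15 minutes. The article sets d = 0.65 for the exercise duration completed, which is the capped outcome itself. To discount it again is to apply it to an uncapped quantity that the article never uses. The discount would also need a standard deviation and a proportion finishing, and the article gives neither.
- A reader might take 65% to 70% as the trial's actual power. It is power conditional on d = 0.65, not a statement about the true effect.

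**Conclusion.** The sample-size statement is wrong on its own inputs. Those inputs require 39 evaluable per group, or 44 randomised per group with 10% dropout, against the 30 given. At d = 0.65 the planned 60 participants provide 69.7% two-tailed power with no loss and 65.0% with 54 evaluable, not 80%.

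The conclusion rests only on figures in the article and on the standard power calculation for the named test. The 65.0% figure also assumes that the full 10% loss occurs and that losses are left out under the complete-case rule. Whether d = 0.65 is itself realistic is not judged here. The error should be corrected before results are reported, because the calculation and the description of the sample as adequate both overstate what a null result would show.

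**What to change.** In Sample size {19}, replace the statement that 30 per group is required with what 60 participants provide. Suggested content:

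- With an independent-samples t test at two-tailed alpha 0.05, 30 per group gives about 70% power for d = 0.65, and about 65% if 10% are lost and 54 are evaluable.
- Power of 80% is reached for d of about 0.74 with 60 evaluable, or about 0.78 with 54. Present these as the effects the sample can detect, not as justified target effects.
- To reach 80% power at d = 0.65, 39 evaluable per group (44 randomised per group, 88 in total) would be needed.

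In Future directions and expected outcomes, remove the description of the sample as adequate or qualify it with the restated power.

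No change in enrolment is needed to make the statement correct. The only cost is a less favourable stated power.

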### Recruitment {20}

Participants will be identified through medical record review based on inclusion criteria. After preselection, patients will be invited to participate, receive detailed information about objectives and procedures and provide written informed consent. A complete clinical assessment will follow, including demographic/sociodemographic data, history, medications, key complementary exams and physical examination. The Hospital Anxiety and Depression Scale (HADS) [24, 25] will be administered. Participants will then be randomized to intervention or control.

### Assignment of interventions: randomization

#### Sequence generation: who will generate the sequence {21a}

The allocation sequence will be generated using a computerized random number generator within the secure REDCap (Research Electronic Data Capture) platform. The sequence will be prepared by an external biostatistician who is not involved in patient recruitment or study procedures.

#### Sequence generation: type of randomization {21b}

Participants will be randomized individually using a computer-generated block randomization sequence with a 1:1 allocation ratio to intervention or control group. Block randomization (fixed block size of 4) ensures balanced group sizes throughout the trial. No stratification will be used. Only the statistician responsible for sequence generation will have access prior to study start.

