### Characteristics of the people who are needed for the trial

**Table Taba:** 

**Characteristic**	**The people we would expect to see included**
Age	Adults aged ≥ 18 years Data to be collected and reported: ● Mean age (years) ● Median age (years) ● Standard deviation ● Range (minimum and maximum age) ● Age distribution by group (intervention vs. control)
Sex	● All sexes eligible ● Data collection method: Self-reported biological sex ● Categories: Male, Female, Intersex
Gender	● All gender identities ● Data collection method: Optional self-report during informed consent process ● Categories to report: Man, Woman or any other gender identities as reported by participants
Race, ethnicity and ancestry	● All races and ethnicities ● Data collection method: Self-reported using Brazilian census categories Categories used (Brazilian IBGE classification): o White o Black o Brown/Mixed race o Asian o Indigenous o Did not declare
Socioeconomic status	● All socioeconomic backgrounds ● Data collection method: Self-reported during baseline assessment ● Socioeconomic indicators to collect: o Education level: Primary education, Secondary education, University degree, Postgraduate degree, No formal education o Employment status: Employed full-time, Employed part-time, Unemployed, Retired, Informal work, Unable to work due to illness o Health insurance type: Public (SUS—Unified Health System), Private health insurance, Both public and private
Geographic location	● Study setting: Single-center urban hospital in Brazil ● Recruitment location details: o Country: Brazil o City: São Paulo o Institution: Hospital São Paulo (Federal University of São Paulo—UNIFESP) o Clinical units: Inpatient Cardiology Unit and Cardiac Surgery Unit
Other characteristics relevant to the trial	● Clinical diagnosis of HF with left ventricular ejection fraction (LVEF) ≤ 50% confirmed by echocardiography

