#### Implementation {23}

Assignment to interventions will be carried out by an external biostatistician using a pre-generated randomization sequence, ensuring impartial and concealed allocation to control or VR intervention groups. Randomization will occur after informed consent is obtained and baseline assessments are completed, preventing selection bias. The biostatistician responsible for randomization sequence generation, concealment and allocation has no direct contact with study participants, no involvement in participant recruitment or eligibility screening, no role in intervention delivery or supervision and no access to outcome data during trial conduct. This individual’s sole responsibility is generating the randomization sequence using appropriate methodology (block randomization with 1:1 allocation ratio), maintaining allocation concealment via secure electronic system and revealing allocation assignments only after participant informed consent and baseline assessment completion.

All randomization activities are conducted remotely via secure electronic communication (REDCap platform with restricted access). Participants and trial staff will not be able to predict or influence allocation assignments, as the randomization sequence is generated remotely and revealed only at the designated time. Physical separation of randomization personnel from clinical trial conduct ensures complete independence and minimizes risk of selection bias or allocation manipulation. The external biostatistician will maintain the randomization sequence in a secure.

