### Assignment of interventions: blinding

#### Who will be blinded {24a}

##### Blinding limitations

Due to the nature of the VR intervention, participants and the physiotherapist cannot be blinded. Participants will necessarily be aware of whether they are receiving standard exercise or VR-augmented exercise, as the presence or absence of the immersive VR headset is inherently visible. Similarly, the physiotherapist delivering the intervention must know group allocation to deliver the assigned intervention appropriately.

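### Fixed blocks of 4, published during recruitment at one unblinded site, let staff who follow the sequence know about a third of allocations in advance, contrary to the protocol's claim of unpredictability

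*Protocol article*

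**What the plan says.** Section {21b} of the protocol article describes a "computer-generated block randomization sequence with a 1:1 allocation ratio to intervention or control group", and adds that "Block randomization (fixed block size of 4) ensures balanced group sizes throughout the trial" and that "No stratification will be used". The participant table under Trial setting gives "Study setting: Single-center urban hospital in Brazil". With 60 participants planned (Sample size {19}), the sequence is a single run of 15 blocks, each holding two VR and two control places.

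The section on blinding limitations says "Due to the nature of the VR intervention, participants and the physiotherapist cannot be blinded" and that "the presence or absence of the immersive VR headset is inherently visible". Section {22} has the research team screen, enrol and collect data. The section on analysis of harms has adverse events documented by participant sequence and arm while recruitment is running, and the section on data quality control has monthly team meetings that go through the exercise logs.

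Section {23} then says "Participants and trial staff will not be able to predict or influence allocation assignments". Its reason is that the sequence is generated remotely and each assignment is released only after consent and baseline assessment.

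**The concern.** Concealing the list and making the sequence unpredictable are separate properties. A secure remote list stops staff from reading the next assignment. It does not stop them from deducing it when they know the block size and can see what has already been allocated. The article gives the block size, and it is dated 28 January 2026, inside a recruitment period planned from 10 November 2025 to 10 November 2026. The size is therefore public for roughly nine of the twelve months.

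Withholding the assignment until after consent and baseline does not close the gap, because a prediction acts earlier: on whom to invite after the record review in {20}, on when to invite them, and on judgement calls such as medical clearance. NYHA classes I to IV are all eligible, so expected exercise time varies widely between candidates. If fitter patients are approached when one arm is expected, the primary outcome is biased directly. Blinding the analyst cannot repair that. The primary comparison in {27a} is an unadjusted t test or Mann–Whitney test on 60 participants.

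**Working it through.** **Inputs.** Block size 4, ratio 1:1, no stratification ({21b}); one centre (participant table); 60 participants ({19}), so 60/4 = 15 blocks. The protocol gives no predictability figure to reproduce.

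**Assumption.** The observer knows the block size and every earlier allocation in order.

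**One block.** With V for VR and C for control, six orders are equally likely: VVCC, VCVC, VCCV, CVVC, CVCV, CCVV. A place is certain when one arm has already used both of its places. The best guess is the arm with more places left.

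| Place | Chance it is certain | Chance the best guess is right |
|---|---|---|
| 1 | 0 | 1/2 |
| 2 | 0 | 2/3 |
| 3 | 2/6 = 1/3 (VVCC, CCVV) | 1/3 × 1 + 2/3 × 1/2 = 2/3 |
| 4 | 1 | 1 |

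- Certain share: (0 + 0 + 1/3 + 1)/4 = 1/3 = 33.3%.
- Correct guesses: (1/2 + 2/3 + 2/3 + 1)/4 = 17/24 = 70.8%, against 50% under simple randomization.

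**Whole trial.** Each block has one certain place, plus a second with probability 1/3. The number certain among 60 is 15 + Binomial(15, 1/3): mean 15 + 5 = 20, SD √(15 × 1/3 × 2/3) = 1.8, minimum 15, maximum 30. The probability of 17 to 23 inclusive is 0.969 − 0.019 = 0.95.

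**What different blocks would do.** Fixed blocks come from exact enumeration. Varying blocks come from 2,000 simulated trials of 60, with an observer who follows every allocation and knows the set of sizes but not their order.

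| Scheme | Certain | Guessed correctly |
|---|---|---|
| Fixed 4 (protocol) | 33.3% | 70.8% |
| Fixed 6 | 25% | 68.3% |
| Fixed 8 | 20% | 66.6% |
| Random 4 or 6 | about 6% | about 69% |
| Random 4, 6 or 8 | about 2% | about 68% |
| Simple randomization | 0% | 50% |

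**Possible bias (illustrative).** The protocol has no figure for steering, so assume that staff enrol patients whose expected exercise time is h SD higher when they predict VR and h SD lower when they predict control.

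- Acting only on certain places shifts each arm by h/3, so the difference shifts by 2h/3 = 0.67h.
- Acting on every untied guess gives a net shift per block of 0 + (2/3 − 1/3) + 1/3 + 1 = 5/3, or 5/12 per place. The difference shifts by 2 × 5h/12 = 0.83h.
- For h from 0.1 to 0.5 SD, the two cases together span 0.07 to 0.42 SD, against the 0.65 SD assumed in {19}.

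**The case against.** The fairest reply is that the one-third figure is conditional. It needs someone who chooses whom to approach, knows the block size, and holds a complete ordered record. The headset is stated to be visible to the participant and the treating physiotherapist, while consent is taken by the principal investigator or coordinators. No section says that those who enrol keep count. The figure of 20 is also an average, with a range of 15 to 30. Section {24b} keeps the hypotheses from participants and the physiotherapist, which weakens any motive to steer. Candidates come from record review against listed criteria. Finally, {23} gives a reason for its statement, so it could be read as an overstatement rather than two incompatible specifications.

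What stands is that the one-third is an expectation under a stated condition, and that the documents show opportunity rather than conduct. The rest does not remove the problem. Data collection by the enrolling team, logs reviewed in team meetings, and events recorded by sequence and arm put order and allocation in front of the recruiting team. The withholding of hypotheses in {24b} does not extend to the investigators and coordinators who take consent, and the article's section on future directions publishes the expectation that VR will do better. Listed criteria do not guarantee consecutive approach. The reason given in {23} concerns access to the list, which is not how the prediction is made.

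One further point is right and limits the remedy: varying the blocks lowers correct guessing by only about 3 percentage points. The case for the change rests on removing certainty.

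**Conclusion.** The concern holds. With fixed blocks of 4 in one unstratified sequence at one site, and with the arm visible, a third of allocations can be known in advance by someone who tracks them: 20 of 60 expected and at least 15 in every complete sequence. The claim in {23} that staff cannot predict assignments describes a property that this design lacks. The percentages are exact given the assumption about the observer. Whether anyone counts, and how far patients would be steered, cannot be settled from the documents; the bias range of 0.07 to 0.42 SD depends on an assumed steering effect. The weakness is real and cheap to reduce, and it should be corrected.

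**What to change.** - The external biostatistician who already holds the list regenerates the part not yet used in REDCap, after completing the current block, with randomly varying block sizes (for example 4, 6 and 8).
- The sizes are kept from the site and from public amendment texts, and reported only with the results.
- The sentence in {23} is amended to say that the list is concealed and the block sizes vary and are undisclosed, instead of claiming that prediction is impossible. The related statements in {23}, on preventing selection bias, and under Measures to minimize bias in {24a}, on staff not knowing the assignment before baseline, should be softened to match.

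**Cost.** One new list and a short amendment through the route in {31}. The final split may differ slightly from 30:30: if recruitment stops inside a block of 8, the arms differ by at most 4. Guessing better than chance is reduced, not removed. Only simple randomization would remove it, at the price of uncontrolled arm sizes (SD of √(60 × 1/2 × 1/2) = 3.9 participants per arm over a full 60). The change cannot help participants already randomized, so the trial report should state the block sizes used and when they changed.
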